### Outcome measures

2.5

#### Primary outcome measures

2.5.1

*Fundus fluorescein angiography*. Inspection method: Tobiconamide eye drops in the conjunctival sac are fully dilated. Perform allergy tests on patients according to reagent requirements. If you are not allergic, push the sodium fluorescein stock solution into the vein and observe the patient's retinal vein filling with the fundus camera. Check before and after treatment.

#### Secondary outcome measures

2.5.2

Observe the best corrected vision before and after treatment. Check with international standard eye chart. The visual acuity chart is 5 m away from the subject. During the inspection, the two eyes are performed separately. One eye is covered. Observe the changes of the fundus before and after treatment. Tobicalamide eye drops in the conjunctival sac were fully dilated, and the fundus camera was used to photograph the patient's fundus.

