### Statistical analysis

2.8

According to the m-ITT principle, all randomized cases will be included. And there is at least one treatment and one post-baseline data. The missing data are not filled, and the actual observation values are used for statistical analysis. The measurement data are described by mean, standard deviation, median, and quartile. If the data meets the normal distribution, it is compared with the baseline value at the time of enrollment, and a paired *t* test is used. Differences in efficacy between the two groups will be compared using independent sample *t* tests. If the normal distribution is not satisfied, a non-parametric test is used. The count data is described using a composition ratio. If the normal distribution is satisfied, the changes before and after treatment in the two groups are tested by *X*^2^. If the normal distribution is not satisfied, a non-parametric test is used. The statistical software is SPSS 24.0, when *P* < .05, it showed that the difference is statistically significant.

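### The recording scale for best corrected visual acuity is not stated; if it is decimal, acuity should be converted to logMAR before changes are calculated and tested

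*Protocol article*

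**What the plan says.** Section 2.5.2 (Secondary outcome measures) of the protocol article sets the outcome as "Observe the best corrected vision before and after treatment". The instrument and distance follow: "Check with international standard eye chart" and "The visual acuity chart is 5 m away from the subject". The notation (decimal, fraction, five-grade logarithmic or logMAR) is not given, and no conversion is mentioned.

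Section 2.8 (Statistical analysis) does not name visual acuity. It has one rule for every continuous outcome:

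- Description: "The measurement data are described by mean, standard deviation, median, and quartile".
- Within group: "If the data meets the normal distribution, it is compared with the baseline value at the time of enrollment, and a paired" t test.
- Between groups: "Differences in efficacy between the two groups will be compared using independent sample" t tests.
- Fallback: "If the normal distribution is not satisfied, a non-parametric test is used".

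Acuity has no rule of its own, so the recorded chart values would pass through this one. Section 2.8 does not say whether the between-group comparison uses change from baseline or the final value.

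**The concern.** An acuity chart can be scored on a scale where equal steps mean equal changes in vision (logMAR or another logarithmic score) or on one where they do not (decimal or fraction). The article fixes the analysis without fixing the scale. With decimals, a gain of 0.1 in an eye that sees poorly is a large improvement, and the same gain in an eye that sees well is small. A mean change in decimals therefore gives more weight to patients with mild loss.

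The stakes are how meaningful the reported acuity change is and how precise the between-group comparison is, in a trial of 64 patients. Acuity is a secondary outcome, but the abstract lists it first among the changes to be observed. Entry admits differing degrees of vision loss (section 2.3.1). If baselines are in fact spread out, the unequal steps matter more; the article gives no acuity distribution.

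**Working it through.** **Inputs from the article.** 32 per group (2.6); dropout up to 20% (2.6), so about 32 × 0.80 = 25.6, or 26 per group, remaining; significance at P < .05 (2.8), taken as two-sided. The article gives no mean, SD, effect or power for acuity, so there is no acuity figure to reproduce.

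**Step 1: size of a decimal step.** The logMAR difference from decimal acuity a to b is log10(b/a), and one line is 0.1 logMAR.

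| Decimal change | Recorded as | logMAR | Lines |
|---|---|---|---|
| 0.1 to 0.2 | +0.1 | log10(2) = 0.301 | 3.0 |
| 0.5 to 0.6 | +0.1 | log10(1.2) = 0.079 | 0.79 |
| 0.9 to 1.0 | +0.1 | log10(1.111) = 0.046 | 0.46 |

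The first step is 0.3010/0.0458 = 6.6 times the last. This is exact, provided that decimals are used.

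**Step 2: whether the fallback removes the problem.** Ranks of final acuity are the same in decimals and logMAR (in reverse order), so a rank test on final values alone is unchanged by conversion. Ranks of change are not the same: 0.1 to 0.2 and 0.9 to 1.0 tie as decimal changes but are far apart as logMAR changes. The mean, SD, median and quartiles of change also stay on the unequal scale.

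**Step 3: power, by simulation.** All acuity inputs are assumptions: baseline logMAR mean 0.4 to 1.0, SD 0.2 to 0.4; SD of change 0.28; common gain 0.1; true difference between groups 0.2; effects additive in logMAR; 32 per group; acuity capped at chart limits. Power for change from baseline:

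| Baseline mean / SD | t test, logMAR | t test, decimal | Mann-Whitney, decimal |
|---|---|---|---|
| 0.4 / 0.2 | 77.6% | 73.2% | 75.0% |
| 0.4 / 0.4 | 72.2% | 65.5% | 68.8% |
| 0.7 / 0.3 | 78.6% | 62.6% | 72.3% |
| 1.0 / 0.2 | 80.5% | 63.2% | 75.6% |
| 1.0 / 0.4 | 79.8% | 48.9% | 67.3% |

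Over the full grid of nine settings, the decimal t test loses about 4 points (77.6 − 73.2 = 4.4) to 31 points (79.8 − 48.9 = 30.9). The rank test on decimal change loses about 3 (77.6 − 75.0 = 2.6) to 13 (79.8 − 67.3 = 12.5). With no true difference, rejection stays near 5% on either scale.

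**Step 4: the plan as written, test choice included.** A Shapiro-Wilk test on one group of 32 rejected normality of decimal change in about 31% to 99% of samples, so the fallback would often apply. The whole procedure was then simulated: Shapiro-Wilk in each group, then t test or Mann-Whitney. With baseline 0.6 (SD 0.35), change SD 0.22, common gain 0.1, difference 0.15 and 32 per group:

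- logMAR t test: 75%
- decimal t test: 57%
- full plan on decimals: 65%, a loss of 10 points

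Across the settings tried, at 26 to 32 per group, the full plan loses roughly 1 to 13 points and an unconditional decimal t test roughly 3 to 31.

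**Step 5: final values instead of change.** The t-test loss in the Step 3 settings is then about −1 to 11 points, and the rank test loses nothing.

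**The case against.** The article never says that acuity is recorded in decimals. With a logarithmic score the problem disappears. That stands, and it makes the point conditional.

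A reader might infer something stronger: that the plan is simply to average and t-test decimal acuities, and that a large part of the power is thereby lost. The article does not support that. Its t tests depend on normality, it reports medians and quartiles as well as means, and it has a non-parametric fallback that skewed decimal changes would often trigger. The larger losses in Steps 3 and 4 belong to an unconditional t test, which is not the stated plan. No loss of power can be established from the article, because it gives no SD or effect for acuity. The simulations also assume effects additive in logMAR, which favours logMAR by construction. If final values were compared by ranks, nothing would be lost.

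It can also be said that variable derivations are commonly left to an analysis plan or full protocol, neither of which is shown. This has some force, but section 2.8 does state how measurement data are handled, and that rule applied to decimal changes would give unequal weight to equal changes in vision. The point is a better method for a stated analysis, not a request for omitted detail.

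Finally, acuity is secondary, the primary outcome is fluorescein angiography, and the sample size is not built on acuity. That limits the weight of the point.

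**Conclusion.** The point holds in conditional form. The recording scale is unstated, and the generic rule in 2.8 would analyse whatever is recorded. If that is decimal acuity, change scores are on an unequal scale, with steps of the same nominal size differing by a factor of up to about 6.6 between 0.1 and 1.0, and the rank fallback on change does not correct this.

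The likely cost under the plan as written is modest: roughly 1 to 13 points of power. This rests on decimal notation, comparison of changes, baseline logMAR 0.4 to 1.0 (SD 0.2 to 0.4), change SD 0.22 to 0.28, a difference of 0.15 to 0.20, effects additive in logMAR, and 26 to 32 per group. There is no added risk of a false positive. It is a low-cost improvement to a secondary outcome, not a flaw that threatens the trial's main conclusion.

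**What to change.** In 2.5.2, state the scale on which best corrected acuity is recorded. In 2.8, add that, unless the scale is already logarithmic, each acuity is converted to logMAR (minus log10 of the decimal acuity) before any mean, change or test is calculated. The existing normality check and non-parametric fallback can then be applied to the logMAR values.

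The cost is a sentence in each section and one transformation in the data file, with no new data or extra visits. If the chart is already scored logarithmically, only the statement of the scale is needed and the analysis is unchanged.

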#### Efficacy evaluation

2.5.3

Refer to “Guidelines for Clinical Research of New Chinese Medicine”. Efficacy was evaluated by the ratio of the difference between the points before and after treatment compared to the points before treatment. Syndrome treatment efficiency (%) = (total points before treatment total points after treatment)/total points before treatment × 100.

(1)Clinical control: clinical symptoms and signs disappeared or basically disappeared, and syndrome scores were reduced by ≥95%;(2)Significant effect: clinical symptoms and signs were significantly improved, and syndrome scores were reduced by 70%;(3)The signs and symptoms have improved, and the syndrome scores have decreased by ≥30%;(4)Ineffective: the clinical symptoms and signs have not improved significantly, and the syndrome scores have decreased by <30%.

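### Syndrome efficacy exists in two forms, a percentage fall and four grades cut from it, and the plan does not say which one is compared between arms

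*Protocol article*

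**What the plan says.** Protocol article, section 2.5.3 (Efficacy evaluation), starts from a quantity measured on every patient: "Efficacy was evaluated by the ratio of the difference between the points before and after treatment compared to the points before treatment". The same section then cuts that percentage into four grades:

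- clinical control: "and syndrome scores were reduced by ≥95" per cent;
- significant effect: "clinical symptoms and signs were significantly improved, and syndrome scores were reduced by 70" per cent;
- a third, improved grade: "The signs and symptoms have improved, and the syndrome scores have decreased by ≥30" per cent;
- ineffective: "the clinical symptoms and signs have not improved significantly, and the syndrome scores have decreased by <30" per cent.

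Section 2.8 (Statistical analysis) gives two routes that could apply. For the first, "Differences in efficacy between the two groups will be compared using independent sample" t tests, with a non-parametric test if the data are not normal. For the second, "The count data is described using a composition ratio", and changes in count data go to chi-square, or to a non-parametric test if normality fails. The significance threshold is P < .05 throughout.

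Section 2.5.1 makes fluorescein angiography the primary outcome. Section 2.5.2 lists best corrected vision and fundus changes as secondary. The syndrome measure has its own heading and is ranked as neither.

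**The concern.** In section 2.5.3 the word efficacy covers both the percentage and the grade. When section 2.8 says that efficacy is compared between groups, the reader cannot tell which is meant. Two things follow.

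First, the routes differ in power. Grading discards information already collected. For a patient starting at an assumed 20 points, ending at 14 (a 30% fall) or at 7 (a 65% fall) gives the same grade, although the results are 7 points apart. Ending at 15 (a 25% fall) gives a different grade from ending at 14, although those are 1 point apart. An unordered test on the grades also ignores their order.

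Second, one outcome with two unranked versions, each testable at P < .05, lets the more favourable version become the reported efficacy result.

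**Working it through.** **What can be reproduced.** The protocol gives no power, effect size, SD or scale range for the syndrome score, so there is no stated power figure to reproduce. From the documents come 32 patients per arm (2.4, 2.6), the cut-offs 30, 70 and 95% (2.5.3, reading the 70% cut as 70% or more) and the 0.05 threshold (2.8, taken as two-sided). Everything else below is assumed.

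**Check 1: simulated point scores.** Scores are integers floored at 0, with grades taken from the percentage fall alone. Inputs: baseline mean 15, SD 4, residual SD 3.5 points, mean falls 45% v 63%, 32 per arm.

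| Between-arm test | Power |
|---|---|
| Chi-square on four grades | 0.51 |
| Rank test (Mann-Whitney) on four grades | 0.69 |
| t test on uncut percentage fall | 0.77 |
| ANCOVA: points after, adjusted for points before | 0.84 |

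Differences in power:
- Grading with an ordered test: 0.77 − 0.69 = 0.08.
- Ignoring the order as well: 0.69 − 0.51 = 0.18.
- Chi-square against the uncut t test, in total: 0.77 − 0.51 = 0.26.
- Baseline-adjusted points against the percentage: 0.84 − 0.77 = 0.07. This gain is separate from grading.

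Over the assumed inputs tried, the ranges were about 0.51-0.57, 0.69-0.75, 0.77-0.82 and 0.84-0.88, in the same order. With 20% dropout (32 × 0.8 = 25.6, about 26 per arm), one set of runs gave 0.41, 0.62, 0.68 and 0.76.

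**Check 2: a different model.** The percentage fall is drawn as normal, capped at 100%, with control mean 30-60% and SD 20-30. The effect is set for 80% power of the uncut t test by the normal approximation, d = (1.960 + 0.842) × √(2/n):
- n = 32: 2.802 × 0.250 = 0.70
- n = 26: 2.802 × 0.277 = 0.78

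| Test | 32 per arm, d = 0.70 | 26 per arm, d = 0.78 |
|---|---|---|
| t test, uncut percentage | 75-81% | 76-80% |
| Rank test on four grades | 64-74% | 63-73% |
| Chi-square on four grades | 45-55% | 44-55% |

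Compared within each scenario, chi-square on the grades loses about 22-34 points against the uncut t test, and a rank test on the grades loses about 4-17. Simulation error is about 1.3 points per figure (1,500 trials per scenario).

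**Check 3: two versions of one outcome.** With no true difference, each test alone rejects in about 4-5% of simulated trials. Counting the result as positive when either the chi-square on grades or the t test on the percentage reaches P < .05 gave 6.5% in one set of runs and about 7.8% in another. Two independent tests would give 1 − 0.95² = 9.75%. The rise is smaller here because both tests use the same scores.

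**The case against.** A reader might infer that the protocol analyses syndrome efficacy as count data by chi-square and so gives up about 26 points of power. The documents do not support that:

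- Section 2.8 never assigns the four grades to the count-data route. Its chi-square sentence concerns changes before and after treatment, and it is conditional on normality, which four grades cannot satisfy. Read literally, it would send them to a non-parametric test.
- The opening sentence of 2.5.3 defines efficacy as the uncut ratio, and the t test sentence in 2.8 fits that ratio. On this reading grading costs no power.
- Most of the 26 points comes from ignoring order, which is a choice of test. Grading itself, with an ordered test, costs 8 points in the worked case and 4-17 in the second model.
- Every power figure rests on assumed means, SDs and effects. The simulations also grade on the score alone, whereas 2.5.3 attaches a description of symptoms and signs to each grade.
- The measure is neither primary nor the basis of the sample size, the grades come from a named guideline, and the exact test for such a measure is often left to an analysis plan that is not shown here.

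All of this stands, and it limits the point. It does not remove it. The uncut-percentage reading is plausible but not stated, the grades are defined under the same efficacy heading, and 2.8 itself offers tests for both forms without choosing.

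**Conclusion.** The point holds as an ambiguity about the analysed variable. It is not a demonstrated loss of power. Depending on the route taken, power at 32 per arm ranges from about 0.51-0.57 (chi-square on the grades) to about 0.77-0.82 (t test on the uncut percentage), and leaving both open raises the false-positive rate to about 6.5-8%. The levels depend on the assumed inputs. The ordering of chi-square, rank test and uncut t test was the same in every scenario run, under two different models.

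The further gain from baseline adjustment (about 0.84-0.88) was examined only in the first model. That model sets the residual variation in points, a structure that suits an analysis in points, so the size of this gain is less secure.

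The consequence is limited: the outcome is not primary, and no power figure in the protocol is overturned.

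**What to change.** In sections 2.5.3 and 2.8, name the post-treatment syndrome score adjusted for the pre-treatment score (ANCOVA) as the single between-arm test of syndrome efficacy, reported as a difference in points with its 95% CI. Keep the four guideline grades as a descriptive table by arm, without a significance test.

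This is a change of wording. It needs no new data, visits or patients. The downside is that the headline becomes a difference in points, which is less familiar to readers used to the grade table; that table is still reported alongside.

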### Sample size calculation

2.6

This study is a small sample clinical trial. According to statistical requirements, there are at least 30 cases in each group. Considering that the drop-out rate does not exceed 20%, a total of 64 cases will be collected, of which 32 will be in the intervention group and the other in the control group.

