### Interventions

2.4

The statistically significant minimum sample size for clinical trials requires no less than 30 patients in each group. For the selected cases that met the inclusion criteria and were screened out by the exclusion criteria, the subjects were randomly divided into the intervention group (32 cases) and the control group (32 cases) by random number method.

Control group: Patients in the control group will be treated with Fufang Xueshuantong Capsule (Manufacturer: Guangdong Zhongsheng Pharmaceutical Co., Ltd.; Specification: 0.5 g). Usage: oral, 1.5 g once, three times a day.

Intervention group: This group will be given the TCM prescription-Dan-Hong Hua-Yu oral solution (Guangzhou Baiyunshan Hutchison Huangpu Traditional Chinese Medicine Co., Ltd.) 20 mL/time, oral, three times a day. The composition of Dan-Hong Hua-Yu oral solution is: *Dansheng*, *Honghua*, *Chuanxiong*, *Taoren*, *Danggui*, *Caihu*, *Zhiqiao*.

Each group will take 4 weeks as a course of treatment and three consecutive courses of treatment without any interval during the course of treatment. At the same time, closely monitor the change of the condition in order to control the deterioration of the condition in time.

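### Section 2.6 is inconsistent: 32 per arm does not keep the required 30 per group across the drop-out it allows, up to 20%

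*Protocol article*

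**What the plan says.** Section 2.6 (Sample size calculation) of the protocol article gives the whole justification in a few lines. It sets a floor: "According to statistical requirements, there are at least 30 cases in each group". It then brings in attrition and states the size: "Considering that the drop-out rate does not exceed 20%, a total of 64 cases will be collected". The two arms are to be equal, at 32 patients apiece.

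Section 2.4 (Interventions) repeats the floor in stronger words, "The statistically significant minimum sample size for clinical trials requires no less than 30 patients in each group", and repeats the split: "randomly divided into the intervention group (32 cases) and the control group (32 cases) by random number method".

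Two other sections decide who counts as evaluable.

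- Section 2.8 (Statistical analysis) uses a modified intention-to-treat set with a condition: "And there is at least one treatment and one post-baseline data". On missing values it says: "The missing data are not filled, and the actual observation values are used for statistical analysis".
- Section 2.5.1 gives the timing of the primary outcome, fundus fluorescein angiography, as: "Check before and after treatment".

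**The concern.** Section 2.6 uses drop-out to explain the step from 30 to 32 per group. A reader will therefore take 30 as the number that should remain after losses of up to 20%. An addition of 2 patients to 30 is far too small for that.

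This is the only sample-size justification in the document, and it does not follow from its own inputs. The reader is told that the size meets a statistical requirement after attrition, when over most of the permitted drop-out range it does not.

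The sentence in section 2.4 adds to the problem by presenting the floor as a statistical property. Significance belongs to a result, not to a sample size, and 30 per group carries no guaranteed power.

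**Working it through.** **Inputs, all from the protocol article**

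- Floor: 30 per group (sections 2.4 and 2.6).
- Drop-out allowance: up to 20% (section 2.6).
- Planned size: 64 in total, 32 per group (sections 2.4 and 2.6).
- Missing values not imputed; primary outcome measured before and after treatment (sections 2.8 and 2.5.1).

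**1. Can the planned 64 be reproduced?**

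| Inflation of the floor at 20% | Calculation | Size |
|---|---|---|
| Correct, per arm | 30/(1 − 0.20) = 37.5 | 38 per arm, 76 total |
| Common mistake, per arm | 30 × 1.20 = 36 | 36 per arm, 72 total |
| Correct, on the total | 60/(1 − 0.20) = 75 | 75 total |
| Common mistake, on the total | 60 × 1.20 = 72 | 72 total |

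None gives 64. The planned 32 per arm does match a much smaller allowance: 30/(1 − 0.05) = 31.6, which rounds up to 32.

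**2. What loss does 32 per arm cover?**

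(32 − 30)/32 = 2/32 = 6.25%, about a third of the stated allowance.

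**3. What remains of 32 per arm?**

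| Drop-out | Left per arm, 32 × (1 − d) | Left in total, 64 × (1 − d) | Floor of 30 kept? |
|---|---|---|---|
| 5% | 30.4 | 60.8 | yes |
| 6.25% | 30.0 | 60.0 | yes, exactly |
| 10% | 28.8 | 57.6 | no |
| 15% | 27.2 | 54.4 | no |
| 20% | 25.6 | 51.2 | no, 4–5 short |

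**4. Does the analysis set rescue the floor?**

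Not as described. The primary outcome has no stated assessment between baseline and the end of treatment, and missing values are not filled. A patient lost before the final angiogram therefore has no post-baseline primary value. Figure 1, the schedule, is not shown, so an intermediate assessment cannot be ruled out.

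**5. How likely is the floor to be met? (illustrative)**

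Assume that patients drop out independently, with the same probability in both arms.

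- At 20%: P(Binomial(32, 0.20) ≤ 2) = 0.032 for one arm, and 0.032² ≈ 0.001 for both.
- At 10%: about 13% for both arms.

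The first line puts the expected rate at the ceiling, so it is the worst case that the plan allows.

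**6. What does the shortfall do to the detectable difference? (illustrative)**

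The document gives no effect size, standard deviation or power, and the scale of the primary outcome is not stated. Assume a continuous endpoint, a two-sample t test, two-sided alpha 0.05 and 80% power. The detectable standardised difference is then about 0.71 at 32 per arm, 0.74 at 30 per arm and 0.80 at 25.6 per arm.

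**The case against.** **The 20% is a ceiling, not a forecast.** This stands in part. Losses of 0 to 2 per arm satisfy every statement in section 2.6, so a reader who infers that the trial will end with 25–26 per arm goes too far. But a size justified by reference to a ceiling should hold at that ceiling, and this one fails from 6.25% upwards.

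**The 30 might mean patients enrolled.** This is weak. Drop-out is the only reason given for going from 30 to 32, and on this reading that clause would have no purpose.

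**The article condenses a fuller plan.** This does not answer the point. Nothing is missing here: the inputs and the result are both printed, and they disagree.

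**The practical harm is limited.** This stands. On the illustrative assumptions, falling from 30 to about 25–26 per arm moves the detectable difference only from 0.74 to 0.80 SD. Even with the floor fully kept, only large differences could be detected. Most of any weakness in power comes from choosing 30 without an effect size, not from the drop-out arithmetic.

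**A null result would be over-read.** A reader might infer this, or conclude that the protocol must call itself exploratory. The document does not say how a non-significant result will be read, and section 2.6 already describes the trial as small. Neither inference is supported as a finding.

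**Conclusion.** The inconsistency is real and rests only on the protocol's own figures. A floor of 30 per group, drop-out of up to 20% and 32 per group cannot all hold. At the ceiling the shortfall is 4–5 per arm, with about 51 of 64 evaluable. Below a loss of 6.25% there is none.

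This assumes that 30 is the number to be retained, and that a patient lost before the final angiogram contributes no primary outcome value. The probabilities and detectable differences are illustrations on added assumptions, and the conclusion does not depend on them.

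Two stronger readings are not supported. One is that the protocol misses a stated power target: it states none. The other is that the trial must enrol 76: that follows only if both the floor and the 20% allowance are kept.

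Severity is moderate. The stated justification is wrong as written, but correcting it need not change patient numbers, conduct or analysis.

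**What to change.** 1. **Section 2.6.** Keep N = 64 and restate what it delivers, for example: *64 randomised (32 per arm); 30 evaluable per arm is retained only if drop-out is no more than 6.25% (2 per arm); at 20% drop-out about 25–26 per arm are evaluable.*
2. **Section 2.4.** Delete the sentence that presents 30 per group as a statistically significant minimum.
3. **If a detectable difference is added**, label it with its assumptions: continuous endpoint, two-sample t test, two-sided alpha 0.05 and 80% power. The protocol states none of these as a basis for sizing, so the figure should not be printed without them.
4. **Alternative.** If the sponsor wants to keep both 30 per arm and a 20% allowance, plan 38 per arm, 76 in total.

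Items 1 to 3 cost a few sentences and a less favourable stated figure, with no extra patients. Item 4 costs 12 more patients (76 − 64) and an extension of the randomisation list, which section 2.7 numbers 1 to 64.
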